### Recruitment strategies

Qualified patients will be recruited by Shanghai Third Rehabilitation Hospital Affiliated to Shanghai University of Traditional Chinese Medicine in Shanghai. The hospital will publish research advertisements to recruit patients. Clinicians will recruit patients strictly following the inclusion and exclusion criteria set in this study. To improve recruitment quality and efficiency, investigators will monitor medical records. The investigators will carefully ask about the patient's past and current medical history, as well as the information related to the experiment, and record it in detail. Patients will be fully informed of the study details.

### Research groups

Control group: conventional rehabilitation + rTMS.

The conventional rehabilitation treatments include physiotherapy therapy, occupational therapy and drug therapy. High-frequency rTMS will be used on the affected side of the primary motor cortex (M1).

Experimental group: conventional rehabilitation + rTMS + Tui Na.

In addition to the conventional rehabilitation treatment and high-frequency rTMS provided to the patients in the control group, the patients will receive Tui Na on the spine and hemiplegic side of UL.

### Randomization and blinding

A simple randomization method will be used in this experiment. Individuals recruited in the experiment will be divided into two groups. Ninety random numbers will be generated by Excel and the random distribution table will be determined by sorting method. In this study, the envelope random allocation method will be used to put the cards printed with the allocation group into sequentially coded, opaque and sealed envelopes one by one according to the random distribution sequence. When the researchers determined that the subjects are qualified, a researcher who did not participate in the treatment, evaluation and statistics opened the envelopes sequentially and assigned the subjects to an appropriate group. An experienced blinded therapist will perform the assessment, he/she is one of the clinical therapists in the hospital. Emergency unblinding will be performed if a serious adverse event occurs. In the event of unblinding during the study, the involved subject will be removed from the study protocol. After trial completion, participant grouping will be revealed, and data analysis will commence. The research data will be properly preserved by specialized researcher. The blind data and the database will be submitted to experimental statistics professionals for statistical analysis and statistical analysis report will be written. After the statistical report is completed, the principal researcher will write a summary report of the research.

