### Inclusion criteria

People will be eligible for inclusion if they meet the following criteria: (1) First ever unilateral ischemic stroke diagnosed by imaging and the course of the disease ranged from 2 weeks to 6 months. (2) UL dysfunction as indicated by the Fugl-Meyer motor function score ≥20-40/66. (3) Aged 40–70 years, regardless of sex. (4) No severe cognitive or communication impairment as indicated by the Mini-mental state examination (MMSE) ≥ 24 points.

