### Sample size calculation

The main purpose of the experiment is to compare whether the curative effect of the experimental group is better than that of the control group. The main evaluation index of curative effect will be the change of upper limb Fugl-Meyer scale. The calculation of the sample size will be based on data from previous research and our previous experiment (18). As the study involves two groups, the sample size calculation formula for a two-sample mean comparison is as follows:

(1)
$$\begin{array}{l} n_{c}=\frac{{\left(z_{1-\alpha }+z_{1-\beta }\right)}^{2}\sigma^{2}\left(1+\frac{1}{K}\right)}{{\left(\mu_{T}-\mu_{C}-\Delta \right)}^{2}} \end{array}$$

where, Z_1_-α = 1.960, Z_1_-β = 0.842, σ = 2.0 (standard deviation), K = 1(ratio of participants in the experimental and control groups), 1 = 3 (optimality bounds), α = 0.025 (2.5% one-tailed significance level), and β = 0.20 (80% power), μ_T_ = 6.6 (predicted mean in experimental group); μ_C_ = 2.3 (predicted mean in control group). The calculated required sample size is 38 participants for each group. Assuming the dropout rate is 20%, 45 participants per group (total of 90 participants) need to be recruited.

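### Time since stroke is neither balanced at allocation nor fixed as a covariate; this costs precision and credibility but does not bias the comparison

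*Protocol article*

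**What the plan says.** Under Randomization and blinding, the protocol article says "A simple randomization method will be used in this experiment" and "Ninety random numbers will be generated by Excel and the random distribution table will be determined by sorting method". Allocation is concealed in envelopes opened in order. No stratification factor or blocking is mentioned.

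Under Inclusion criteria, patients qualify with a first unilateral ischemic stroke where "the course of the disease ranged from 2 weeks to 6 months".

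Under Sample size calculation, "The main evaluation index of curative effect will be the change of upper limb Fugl-Meyer scale". The planned mean changes are 6.6 and 2.3, the SD is given as "σ = 2.0 (standard deviation", and the superiority bound is 3.

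Under Efficacy analysis, the arms are compared by t-test or, failing normality or equal variances, by the Wilcoxon rank sum test. Neither is adjusted. Under Comparability analysis, a baseline variable becomes a covariate only if the arms differ on it significantly and the difference is judged relevant on professional grounds. The variables named are sex, Fugl-Meyer-UE, muscle strength, MBI, MEP and the fNIRS measures. The list of continuous variables is open-ended, but time since onset is not on it.

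**The concern.** The eligibility window is wide: 26 weeks at one end is thirteen times 2 weeks at the other. If natural recovery of the upper limb depends on time since stroke, that time explains part of the spread in the change score in both arms. Unstratified allocation leaves its balance to chance, and the analysis then leaves its share of the variance in the error term.

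The rule in Comparability analysis is a weak safeguard. A moderate imbalance in a prognostic variable will usually not reach significance with 45 per arm, so it would go unadjusted. Two things are at stake: power that could be had for nothing, and how convincing the result looks if the arms turn out visibly different in how long ago their patients had their strokes.

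**Working it through.** **Inputs from the protocol article.** SD 2.0; planned changes 6.6 and 2.3; bound 3; one-sided α 0.025 (z = 1.960); 80% power (z = 0.842); 45 recruited per arm; 20% dropout.

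**Assumptions not in the documents.** Half the patients are early and half late; the two halves differ by D points in natural change; the arms are 45:45, as a sorted list of 90 would allow.

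**1. The plan's own figure.** n = (1.960 + 0.842)² × 2.0² × 2 / (6.6 − 2.3 − 3)² = 62.81 / 1.69 = 37.17, rounded up to 38 per group, as stated. The planned difference is 4.3 points, and the trial is powered on 4.3 − 3 = 1.3 points above the bound.

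**2. Chance imbalance in the share of early patients.** With 90 patients, 45 early and 45 per arm, the number early in one arm is hypergeometric with variance 45 × 0.5 × 0.5 × 45/89 = 5.69 and SD 2.385. The difference in early share between arms has SD 2 × 2.385/45 = 0.106. A gap of 15 percentage points or more arises in about 20.6% of allocations, and 20 points or more in about 9.1%.

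**3. Which D is compatible with the protocol.** Two equal halves that differ by D contribute a between-half SD of D/2, so the implied correlation is r = (D/2)/2.0.

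| D | D/2 | r | 95% shift = 1.96 × 0.106 × D | of 4.3 | of 1.3 |
|---|---|---|---|---|---|
| 1 | 0.5 | 0.25 | ±0.21 | 5% | 16% |
| 2 | 1.0 | 0.50 | ±0.42 | 10% | 32% |
| 3 | 1.5 | 0.75 | ±0.62 | 14% | 48% |

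At D = 4, D/2 = 2.0: time since onset alone would account for the whole planned SD. Larger values exceed it. D of 4 or more therefore does not fit the protocol's figures and is not used.

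**4. What adjustment recovers.** The residual SD is 2.0 × √(1 − r²), which at r = 0.5 is 1.73. Normal-approximation power is Φ(1.3 / (SD × √(2/n)) − 1.96).

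- n = 45, unadjusted: 1.3/0.4216 − 1.96 = 1.12, power 86.9%.
- n = 45, adjusted: 1.3/0.3651 − 1.96 = 1.60, power 94.5%.
- n = 36 (45 × 0.8), unadjusted: 1.3/0.4714 − 1.96 = 0.80, power 78.7%.
- n = 36, adjusted: 1.3/0.4082 − 1.96 = 1.22, power 89.0%.

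Over r = 0.3 to 0.7, adjusted power runs from 89.8% to 99.1% at 45 per arm and from 82.4% to 97.1% at 36.

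**The case against.** The strongest reply is that chance imbalance under randomization is not bias. It is part of the sampling error. With SD 2.0 and 45 per arm the standard error is 0.42 and its 95% range is ±0.83 points; any shift due to time since onset lies inside that range and is not added to it. The sample size and the type I error rate already allow for it. This stands in full. A reader might infer that the trial would credit Tui Na with natural recovery; the documents do not support that, because over all allocations the test keeps its nominal error rate.

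A reader might also infer that imbalance could take up a large part of the planned advantage. Against the planned 4.3 points it cannot: even at r = 1 the 95% shift is 0.83 points, or 19%. The share looks substantial only against the 1.3 points above the bound, and then only with a moderate to strong assumed correlation.

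Nor do the documents show that all secondary and fNIRS measures follow the same natural course. They give no figure for how any outcome depends on time since stroke.

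It is also fair that simple randomization is a valid method, that the list of baseline variables is open, and that an analysis plan not shown here might name the covariate. But the article itself fixes unadjusted tests and a significance trigger, so such a plan would have to replace what is stated. Changing the allocation scheme during recruitment is debatable; fixing the analysis is not open to that objection.

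**Conclusion.** The point holds as a free improvement. Allocation is unstratified across a wide onset window, and the primary comparison ignores time since onset unless a baseline test happens to flag it. The cost is precision and the credibility of the one allocation realised.

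At an assumed D = 2 the 95% chance shift is about ±0.42 points. Planned adjustment for time since onset would then take power at 36 completers per arm from just below the 80% target to well above it. These figures rest on half the patients being early, on the assumed D, on the protocol's SD of 2.0, and on a test made against the bound of 3, as the sample size is. A weaker link between onset time and recovery shrinks both the shift and the gain; with no link, adjustment costs next to nothing.

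**What to change.** Name time since onset and baseline Fugl-Meyer-UE as covariates in the primary comparison, regardless of any baseline test; an ANCOVA of the change in Fugl-Meyer-UE is one example. State in advance how time since onset enters (continuous on a given scale, or one cut-point), and fix this before unblinding. For these two variables it replaces the significance-triggered rule in Comparability analysis. The cost is a short amendment and one degree of freedom per covariate entered as a single term. No new data are needed, since time since onset must be known to apply the inclusion criterion and Fugl-Meyer-UE is measured at baseline.

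Optionally, for allocations not yet made, stratify by one onset cut-point, using two envelope series with blocks of varying size. The downsides are slight predictability and two allocation schemes in one trial. The Abstract dates the start of recruitment to 10 February 2022, and screening was planned only to December 2022, so few or no allocations may remain to benefit. The covariate adjustment does not depend on this step.

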### Statistical analysis

#### Data set population determination

In this research, the Intention to treat (ITT) and Per-Protocol set (PPS) will be used together. In line with the selection and exclusion criteria in the program, good compliance, no other related treatment will be carried out during the research, and the case report forms (CRF) table will be completed, which has an evaluable curative effect index. The patients with poor curative effect will be also included in the PPS set as ineffective cases. For missing data, we will use LOCF method to make up. We will use the Statistical Package for Social Sciences (SPSS-IBM^®^,Armonk, NY: IBM Corp.) version 20 for Windows to complete statistical analysis of this study.

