### Statistical analysis plan

#### Case distribution analysis

The shedding and elimination cases will be described, and the drop rate and elimination rate of the two groups will be compared.

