#### Safety analysis

Adverse events and adverse reactions will be analyzed by statistical description method, and chi-square test or exact probability method will be used to compare the incidence of adverse events and adverse reactions between the two groups.

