### Withdrawals

A participant will be withdrawn from the study, because of occurrence of severe adverse events and patient's own factors, for instance having a cerebrovascular accident, seizure, or the subject could not be contacted, or the subject is not willing to continue to join.

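### Removal after unblinding depends on serious adverse events and is not reconciled with the intention-to-treat analysis

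*Protocol article*

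**What the plan says.** Two adjacent sentences in Randomization and blinding form a chain. The first is "Emergency unblinding will be performed if a serious adverse event occurs"; the second is "In the event of unblinding during the study, the involved subject will be removed from the study protocol". The second is not limited to emergency unblinding.

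The Withdrawals section has a parallel rule: "A participant will be withdrawn from the study, because of occurrence of severe adverse events and patient's own factors". Its examples include a new cerebrovascular accident and a seizure, listed beside loss of contact and unwillingness to go on. One section speaks of serious events and the other of severe events, so it is not clear that the two triggers are the same.

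For the analysis, Data set population determination says that "the Intention to treat (ITT) and Per-Protocol set (PPS) will be used together" and, in the same section, "For missing data, we will use LOCF method to make up". Case distribution analysis adds: "The shedding and elimination cases will be described, and the drop rate and elimination rate of the two groups will be compared". Under Safety analysis, a "chi-square test or exact probability method will be used to compare the incidence of adverse events and adverse reactions between the two groups". Table 1 schedules adverse-event recording from the first treatment day to four weeks after treatment ends.

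**The concern.** ITT keeps the randomised groups intact whatever happens afterwards. Here a subject is removed because of an event after randomisation that treatment may influence and that may itself change arm function. If the arms differ in how often this happens, or in how removed subjects would have fared, the comparison is no longer protected by randomisation.

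The article never says what removal means: stopping the study treatment, ending follow-up, or leaving the analysis. Only the first sits easily with ITT. The others put at risk the Fugl-Meyer scores after the event and the adverse events that follow the first one. Measurements not taken cannot be recovered at analysis.

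**Working it through.** **Reading the sections together.** The chain is: serious adverse event, then unblinding, then removal; and separately, severe adverse event, then withdrawal from the study. No section separates the end of treatment from the end of follow-up. No section says that an unblinded subject's data are deleted, and none says that they are kept. That leaves three readings:

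1. Treatment stops, but follow-up and analysis continue. This is compatible with ITT, but it fits poorly with the Withdrawals wording, which concerns the study rather than the treatment.
2. Follow-up stops and the subject stays in ITT. LOCF then supplies the later visits.
3. The subject leaves the analysis. This is not ITT.

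**Inputs.** Sample size calculation gives expected mean changes of 6.6 (experimental) and 2.3 (control), SD 2.0, a bound of 3, one-sided alpha 0.025, 80% power and 45 recruited per group. The planned size before dropout reproduces: (1.960 + 0.842)² × 2.0² × 2 / (6.6 − 2.3 − 3)² = 37.17, so 38 per group. No serious adverse event rate is given, so every rate below is an assumption.

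**Reading 3, deletion.** Take 6.6 and 2.3 as the means of subjects not removed, and assume that removed subjects would show zero change. With fractions qT and qC removed:

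- True ITT difference = (1 − qT) × 6.6 − (1 − qC) × 2.3
- Difference after deletion = 6.6 − 2.3 = 4.3
- Bias = 6.6 qT − 2.3 qC

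| Removed, experimental | Removed, control | Bias (points) |
|---|---|---|
| 2% | 2% | 0.132 − 0.046 = 0.09 |
| 5% | 5% | 0.330 − 0.115 = 0.22 |
| 5% | 2% | 0.330 − 0.046 = 0.28 |
| 10% | 2% | 0.660 − 0.046 = 0.61 |
| 2% | 10% | 0.132 − 0.230 = −0.10 |

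In whole subjects, 2 of 45 in the experimental arm only gives 6.6 × 2/45 = 0.29. With 2 of 45 in each arm it is 0.29 − 2.3 × 2/45 = 0.29 − 0.10 = 0.19. With 2 of 45 in the control arm only it is −0.10.

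**Reading 2, LOCF.** If k of 45 experimental subjects have a carried-forward change c in place of a true change y, the bias in that arm's mean is (k/45) × (c − y). Keep y = 0 and k = 2:

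- Event before the week-2 visit: baseline is carried forward, c = 0, and the bias is 0. The arm mean is 6.6 × 43/45 = 6.31, the same as with full follow-up.
- Event after week 2: c is the gain by then, which the article does not give. If c lies between 0 and 6.6, the bias lies between 0 and 0.29.

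If the event takes a subject below baseline (y < 0), LOCF is biased even when baseline is carried forward.

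**Loss of numbers.** Assumed removal of 1%, 2%, 5% or 10% takes 0.9, 1.8, 4.5 or 9 of 90 subjects. If all left the analysis, power from 45 per group would fall from 86.9% to 86.6%, 86.3%, 85.2% or 83.3%. Precision is hardly affected; the issue is bias.

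**The case against.** The best defence is that the removal sentence speaks of the study protocol, not of the dataset. The article promises ITT and states LOCF, so a withdrawn subject can stay in ITT with a carried-forward value. Removals would also be visible, because drop and elimination rates are compared by arm. Large imbalance is not obviously expected: both arms receive rTMS, the only component for which the Adverse events section mentions seizure, and that section sees no serious risk from Tui Na.

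Much of this stands, and it rules out three stronger readings that a reader might infer.

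- *That the worst outcomes are deleted from the safety analysis.* Safety analysis excludes nobody, adverse events are recorded from the first treatment day, and the triggering event has already happened when unblinding follows. What can be lost is adverse events after removal.
- *That the plan flatly contradicts ITT.* That is true only if removal means leaving the analysis, which the article does not say.
- *That the experimental arm is favoured by a known amount, such as 0.29 points.* That figure needs deletion, zero gain, an assumed count and all events in one arm. Under LOCF it can be zero, and with more events among controls the sign reverses.

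The choice between ITT and per-protocol as the deciding set may also lie in a fuller document, so its absence is not a fault by itself.

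The defence does not remove the defect. The Withdrawals section literally ends study participation for severe events, LOCF is no substitute for observed outcomes after such an event, and comparing removal rates reveals an imbalance without correcting it.

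**Conclusion.** The point holds as a badly fixed rule. Removal depends on a post-randomisation event that may relate to treatment and outcome, and the sections on blinding, withdrawals and analysis sets are not reconciled. Either the ITT set is broken, or later outcomes are replaced by carried-forward scores and later adverse events are missed.

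The size cannot be stated from the article. Under deletion with zero gain in removed subjects, the assumed rates tabulated give −0.10 to 0.61 points, against a planned difference of 4.3 and an excess over the bound of 4.3 − 3 = 1.3. Under LOCF with 2 of 45 affected in the experimental arm only, zero true change and a carried gain of 0 to 6.6, the range is 0 to 0.29. The effect is probably small if events are rare and balanced, and its direction depends on which arm has more of them. It merits correction because uncollected follow-up cannot be restored and the remedy is cheap.

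**What to change.** Replace the removal sentence in Randomization and blinding with text to this effect: unblinding or a serious adverse event does not by itself remove a subject from the ITT or safety analysis; data already collected are kept; and outcome and adverse-event follow-up continues, with analysis in the randomised group, where the subject consents and the investigator considers the assessment appropriate.

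Then reconcile Randomization and blinding, Withdrawals, Data set population determination and Safety analysis:

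- Separate the end of study treatment from the end of follow-up.
- Use one term for the triggering event, or say how serious and severe differ.
- Name ITT (all randomised subjects) as the primary set and the per-protocol set as a sensitivity analysis.

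Whether treatment or any particular procedure stops after an event stays with the investigators. The cost is a wording amendment and a few further assessments of subjects already enrolled; no stated sample size or power figure changes.

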### Outcome measures

The assessment will be conducted on four time points, including at baseline, 2 weeks and 4 weeks after the beginning of the treatment, and 4 weeks after the end of the treatment (Table 1). All assessments will be performed by therapists who do not know the specific group.

**Table 1 T1:** SPIRIT figure.

	**Screening**	**Baseline**	**Intervention**			**Follow weeks**
Time Point	**-t** _ **2** _	**-t** _ **1** _	**0**	**w2**	**w4**	**4w**
Enrollment						
Informed consent	**√**					
Demographic information	**√**					
Medical history	**√**					
MMSE	**√**					
Eligibility assessment	**√**					
Random allocation		**√**				
Interventions						
Tui Na+TMS group						
Cnventional group						
Assessments						
Fugl-Meyer-UE		**√**		**√**	**√**	**√**
MS		**√**		**√**	**√**	**√**
MAS		**√**		**√**	**√**	**√**
MBI		**√**		**√**	**√**	**√**
MEP		**√**		**√**	**√**	**√**
fNIRS		**√**		**√**	**√**	**√**
Adverse event			**√**	**√**	**√**	**√**

Description of the protocol. -t2, first contact with participants; -t1, baseline evaluation;0, starting day of the treatment; w2, 2weeks after the start of treatment;w4, 4 weeks after the start of treatment and post evaluation;4w, 4 weeks after the end of treatment; MMSE, Mini-Mental State Examination; Fugl-Meyer-UE, Fugl-Meyer Upper Extremity Scale; MS, Muscle Strength; MAS, Modified Ashworth, MBI, Modified Barthel Index; MEP, Motor evoked potentials; fNIRS, functional near-infrared spectroscopy; The orange line represents the treatment time in the figure, with a total of 4 weeks of treatment.

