#### Comparability analysis

According to the analysis of the basic situation of the two groups before treatment, the sex of the patient will be divided into two variables, and the chi-square test of two independent sample rates will be used. W-test and F-test will be used to determine that the continuous variables such as Fugl-Meyer-UE, MS, MBI and MEP and fNIRS measurements (Lateral Index, RSFC values, zfALFF values) in the baseline is in accordance with normal distribution and homogeneity of variance, and two independent sample *t*-tests will be used for comparison. If these data do not conform to normal distribution or homogeneity of variance, Wilcoxon rank sum test will be used to compare the measurement data. If the comparison of the variables in the baseline between the two groups is statistically significant and professional, the variable will be analyzed as a covariable multiple efficacy index.

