#### Efficacy analysis

The data in accordance with normal distribution and homogeneity of variance in the main and secondary indicators will be compared with *t*-test to see if the difference between the two groups before and after treatment is statistically significant. The rank data with non-normal distribution or uneven variance will be analyzed by Wilcoxon rank sum test.

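### The protocol reveals the grouping before analysis yet speaks of blind data; the few open judgement calls should be settled before any outcome comparison and before the reveal

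*Protocol article*

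**What the plan says.** All references are to the protocol article.

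- **Order of events** (Randomization and blinding): "After trial completion, participant grouping will be revealed, and data analysis will commence".
- **What the statisticians receive** (same section, two sentences later): "The blind data and the database will be submitted to experimental statistics professionals for statistical analysis and statistical analysis report will be written".
- **Assessors** (Outcome measures): "All assessments will be performed by therapists who do not know the specific group". Assessor blinding is not in dispute.
- **Covariates** (Comparability analysis): adjustment for a baseline variable is made on this condition: "If the comparison of the variables in the baseline between the two groups is statistically significant and professional". The condition has two parts, a significance test and a professional judgement. No criterion is given for the second.
- **Test** (Efficacy analysis): "The data in accordance with normal distribution and homogeneity of variance in the main and secondary indicators will be compared with" a t-test; otherwise, "The rank data with non-normal distribution or uneven variance will be analyzed by Wilcoxon rank sum test".
- **Analysis sets** (Data set population determination): intention-to-treat and per-protocol sets are both used. Per-protocol membership depends partly on good compliance, with no threshold.
- **Lock** (Data security): three parties lock the database. Whether this comes before or after the reveal is not stated.

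**The concern.** The section gives a sequence in which grouping is disclosed and analysis follows, but describes the data handed over as blind. A reader cannot tell whether the statisticians are meant to be masked.

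The control arm receives no sham Tui Na (Research groups), and Tui Na is 30 minutes of hands-on treatment per session (Intervention). The article does not say so, but patients and treating therapists will therefore know the arm. Protection against bias rests on the blinded assessor and on how the analysis is conducted. If the arms are known when imbalances are judged relevant or compliance is judged good, those calls can be influenced by the result they produce, and nothing on record would show that they were not.

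**Working it through.** **1. The two sentences side by side.**

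| Reading of blind data | Consequence |
|---|---|
| Data without arm identity | Conflicts with revealing the grouping before analysis starts |
| The blinding code, handed over with the database | No conflict, but the statisticians know the arms from the start |

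The section needs rewording on either reading.

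**2. Which choices are really open.**

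- t-test or Wilcoxon: a written rule based on normality and variance.
- Whether a covariate may be considered: a written rule based on baseline significance.
- Whether a significant imbalance also counts as professionally relevant: judgement.
- Good compliance for the per-protocol set: judgement.
- Form of the primary outcome: Sample size calculation names the change in the upper limb Fugl-Meyer score. Efficacy analysis speaks only of before and after treatment, but the change score is the stated index.

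**3. Size.** The plan gives no figure on this point to reproduce. The illustrations below simulate trials with no true effect, 45 per arm (from Sample size calculation), tested at two-sided 0.05. All other inputs are assumptions, because the article gives none for them.

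*(a) Written rules applied mechanically.* Normal outcome, one baseline covariate, 10,000 trials per row. The simulation standard error near 5% is √(0.05 × 0.95 / 10,000) = 0.2 percentage points.

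| Assumed baseline-outcome correlation | Fixed t-test | Fixed ANCOVA | Written rule | Smallest p of t-test, Wilcoxon, ANCOVA |
|---|---|---|---|---|
| 0.3 | 5.1% | 4.8% | 4.9% | 7.2% |
| 0.5 | 4.7% | 5.1% | 4.2% | 7.9% |
| 0.7 | 5.2% | 4.9% | 3.9% | 9.1% |

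The written rule does not inflate the error. The last column goes beyond the plan: it lets the analyst ignore the normality rule and adjust without a significant imbalance.

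*(b) Discretion within the plan's own options.* Outcome is the change score. Adjustment for baseline Fugl-Meyer-UE is available only after a significant imbalance, and its use is then free. Assumed: baseline SD 5.8, change SD 4, slope of change on baseline -0.2; 6,000 trials.

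- Free use of the professional judgement: 5.1%.
- Adding free choice of a per-protocol set with 15% removed: about 7%.

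The protocol's own SD is 2.0, so I repeated this with 10,000 trials at each of two change SDs, with the 15% removed at random. SD 2.0 gave 5.3%, then 7.3%. SD 4 gave 5.2%, then 7.4%. The result hardly depends on the SD.

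*(c) What A/B coding does by itself.* Swapping the arm labels turns t into -t, and the two-sided p-value depends only on |t|. Someone holding coded arms can compute the same p-values and choose the smallest. Coding hides direction only. What limits selection is settling the choices before any outcome comparison.

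**The case against.** The strongest defence has four parts.

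- **The sentences may be compatible.** The text names the blind data and the database as separate items, which fits handing over the allocation code with the database. This stands, so a flat contradiction cannot be asserted. The analysis is then unblinded from the start, and the ordering point remains.
- **A statistician who knows the arms after trial completion is common, and no sentence clearly promises a masked one.** This also stands. The weakness is the combination of a stated early reveal, data called blind, and judgement calls left open.
- **Most choices are written rules, and a separate analysis plan may settle the rest.** The first half stands, and step 3(a) supports it. On the second, an unseen plan could define compliance or covariates, but would not change the order written in this article.
- **The database lock already protects the trial.** Only in part: it protects data values, not analysis choices, and its place relative to the reveal is not given.

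A reader might infer a much larger effect, with false positives rising to about 12%. Choosing the best of six analyses in simulation does give 12.1%. The documents do not support that figure for this plan. Its largest step, from 6.3% to 10.2%, comes from a final-score t-test, although Sample size calculation names the change score; without that option the figure is 8.8%. It also treats ANCOVA, and ANCOVA plus age, as always available, whereas Comparability analysis admits a covariate only after a significant imbalance.

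**Conclusion.** The point holds in limited form. Randomization and blinding either contradicts itself or specifies an unblinded analysis. On the stated order, the professional relevance of imbalances and good compliance can be judged with the arms known, in a trial where patients and treating therapists already know them.

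The written rules do not inflate type I error when followed mechanically. Discretion within what the plan offers takes a nominal 5% to roughly 5% to 7%. That range assumes normal data, one candidate covariate, and one alternative per-protocol set with 15% removed at random. It does not model choosing patients one by one in the light of their outcomes, and it is an illustration, not a prediction. Nothing in the article shows that such choices will be made improperly. Assessor blinding is unaffected.

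**What to change.** State one order in Randomization and blinding:

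1. Lock the database, cross-referring to Data security.
2. Before any between-group outcome comparison, settle and document per-protocol membership, the covariates, and the primary test on the change in Fugl-Meyer-UE.
3. Analyse with the groups coded A and B. The code is held by the researcher who opens the envelopes, who by the article's own account takes no part in treatment, evaluation or statistics.
4. Reveal which code is Tui Na only after the statistical report is complete.

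Delete the sentence that puts the reveal before the analysis, and say plainly what the statisticians receive. Any covariate check that needs the two groups compared at baseline can be done with coded arms.

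Step 2 is the essential one. The coding in step 3 is a safeguard and does not replace it. The cost is rewording, a coded group variable and the small extra step of keeping the code. No patients, visits or staff are added.
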